### Sample size

For this NI trial, we calculated an NI margin using guidelines developed by the US Food and Drug Administration and the European Medicines Agency.^35^ Briefly, the NI margin is based on effect sizes from prior meta-analyses or trials of the active control, with the smallest expected treatment effect (M1) set at the limit of the 95% CI that is closest to the null effect. We found no studies comparing the effects of MMS and calcium taken together versus placebo, and data comparing MMS to a placebo were similarly limited. We therefore used the pooled effect size for Hb concentration at or near term (8.88 g/L (95% CI 6.96 to 10.8)) from 20 trials of iron-containing supplements, compared with the same formulations without iron, no treatment or a placebo.^36^ As the lower limit is clinically large (7.0 g/L), common practice is to preserve 50% of the minimum effect for an NI margin (M2) of −3.5 g/L. However, the absolute value of this effect exceeds 3.0 g/L, which we would consider clinically meaningful based on the difference between the third and fifth normative centiles for maternal Hb at 30<34 weeks’ gestation derived from the INTERGROWTH-21st Project,^37^ that is, the difference between a probable diagnosis of being at high risk versus anaemic. Therefore, we selected a more conservative NI margin of −3.0 g/L.

We assumed a one-sided α=0.025; 90% power; an SD of 17 g/L, based on prior data from both sites and assuming equal group variance across treatment arms^38,39^; and 15% loss to follow-up. Accordingly, a sample of 1600 women per country (3200 women in total) will be required to conclude NI, in each country independently; that is, that the lower limit of the 95% CI around the difference in Hb concentration between the intervention (MMS and Ca taken together) versus control (MMS and Ca taken separately) is greater than −3 g/L.

### Participant timeline

The schedule of enrolment, interventions and assessments is summarised in table 3. Participants will be screened, enrolled and followed monthly in the communities in Pakistan and in health facilities in Burkina Faso. Figure 2 presents a draft flow diagram combining both sites. If notable differences in loss to follow-up or exclusions emerge between sites during analysis, separate diagrams will be provided for each country in the trial manuscripts.

**Figure 2 F2:**
[figure not shown]
CaMMS trial flow diagram. CaMMS, calcium and multiple micronutrient supplement.

**Table 3 T3:** Schedule of enrolment, interventions and assessments in the CaMMS trial

	Screening	Allocation	Post-allocation					Close-out
TIMEPOINT^*^	*−t_i_* to t_0_	Baseline: 6<20 weeks	Interim ANC/HH visits	Mid-Pregnancy: 20<24 weeks	Interim ANC/HH visits	Late Pregnancy: 30<34 weeks	Interim ANC/HH visits	Birth
		(t_0_)	(t_1_)	(t_2_)	(t_3_)	(t_4_)	(t_5_)	(t_6_)
ENROLLMENT:								
Screening consent	X							
Eligibility screening (Hb testing; ultrasound)	X							
Trial consent	X							
Allocation		X						
INTERVENTION/ COMPARATOR:								
Ca and MMS Together								
Ca and MMS Separate								
ASSESSMENTS FOR WOMEN:								
Socio-demographics		X						
Food insecurity		X						
Obstetric history		X						
Dietary intake		X		X		X		
Health card data abstraction^†^		X	X	X	X	X	X	X
Anthropometry		X		X		X		
Blood pressure		X		X		X		X
Venous blood draw		X		X		X		
Point-of-care Hb testing		X		X		X		
Adherence			X	X	X	X	X	X
Morbidity		X	X	X	X	X	X	X
Pregnancy outcome								X
ASSESSMENTS FOR INFANTS:								
Anthropometry								X
Heel prick blood sampling								X
Point-of-care Hb & ferritin testing ^‡^								X

* Interim visits include: (a) routine antenatal care in Burkina Faso or household visits in Pakistan, where data will be collected and supplements dispensed; and (b) HH visits to provide counselling and measure adherence. Timepoints will vary depending on week of enrolment (eg, women enrolling at 6 weeks will have three interim ANC and 4 HH visits; women enrolling at 19 weeks will have no interim ANC and 2–3 HH visits).

† Abstracted data will include anthelminthic medications, sulfadoxine-pyrimethamine (Burkina Faso only), low-dose aspirin, blood transfusion, IV iron, iron-containing supplements.

‡ Point of care ferritin testing will be done for infants only.

ANC, Antenatal care; CaMMS, calcium and multiple micronutrient supplement; Hb, haemoglobin; HH, household; MMS, multiple micronutrient supplement.

### Study visits

#### Screening

Women with a positive urine pregnancy test, fundal height<22.5 cm (in Burkina Faso only) and meeting age criteria will be invited to hear about the trial. Those consenting to screening will be asked about willingness to receive antenatal care at study clinics, discontinue IFA for trial supplements and any contradictions. A capillary blood sample will be taken to measure Hb using a HemoCue Hb 301 device (HemoCue AB, Angelholm, Sweden). Women with Hb<70 g/L will not be enrolled but will be referred for treatment. In Burkina Faso, a malaria rapid diagnostic test will be performed concurrently. All women testing positive will be referred for clinical assessment and treatment according to the national and WHO treatment guidelines, that is, quinine in the first trimester and artemisinin-based combination therapies in the second and third trimesters. Burkina Faso implements the intermittent preventive treatment strategy during pregnancy with sulphadoxine-pyrimethamine (SP). All pregnant women will receive at least three doses of SP one month apart, starting at 16 weeks of gestational age. To ensure full compliance with this strategy, we will supply clinics should they run out of SP stock.

Eligible women will then undergo a transabdominal ultrasound (MindRay DP-10 in Burkina Faso or M6 in Pakistan) to confirm viability and intrauterine pregnancy, assess the number of foetuses, and calculate GA via foetal biometry. Three crown-rump-length (CRL), where CRL≤85 mm, or head circumference measurements will be averaged and GA estimated using INTERGROWTH-21st Standards^40^ or, if<8 weeks, the Verburg reference.^41^ Women with a non-viable or extrauterine pregnancy or with any suspected abnormality will be considered ineligible and referred for care.

#### Baseline

Women meeting all eligibility criteria will be asked to undergo the informed consent procedure for the trial. Consenting women will be randomly allocated as described and research staff will complete a baseline form, capturing data on demographics, socioeconomic status,^42^ household food insecurity,^43^ obstetric history, tobacco use (for Pakistan only) and diet. Dietary data will be collected using a semi-quantitative food frequency questionnaire (FFQ) developed using prior 24-hour recalls collected at each site^44
45^ to capture approximately 95% of iron and calcium intake. Portion sizes were standardised by household utensils, bowl sizes, or reference sizes; weight equivalents and visual aids were developed at each site. Because shared meals are common in Burkina Faso, questions on eating alone versus with others were included; in Pakistan, enumerators were trained to address this. The FFQ was pre-tested at both sites before finalisation.

After administering the questionnaire, women will undergo a physical exam, where staff will measure women’s weight to the nearest 100 g using an ADE M316600 electronic floor scale (ADE Germany GmbH, Hamburg, Germany), height to the nearest 1 mm using an ADE MZ10042 mobile stadiometer (ADE Germany GmbH, Hamburg, Germany), mid-upper arm circumference to the nearest 1 mm, and blood pressure using the Microlife Cradle VSA (Microlife, Widnaw, Switzerland). They will then use antecubital venipuncture to collect a venous blood sample into (a) an untreated or serum-separator blood collection tube for serum-based analyses (ferritin; soluble transferrin receptor; hepcidin; erythropoietin; C-reactive protein (CRP); α_1_-acid glycoprotein (AGP)) and (b) an EDTA-treated evacuated blood collection tube for assays requiring whole blood (CBC; haemoglobinopathies; malaria parasitaemia in Pakistan). While the Hb measured by HemoCue at screening will serve as an initial screening for severe anaemia, results of the CBC will be used for the baseline Hb measurement. CBC results will be reviewed to identify any women with Hb<70 g/L who were not flagged by on-site HemoCue testing. For the baseline visit, these women will be contacted to provide a referral and will be treated as post-randomisation exclusions. Blood samples will be stored in insulated containers with cold packs prior to transit to local laboratories for processing. Finally, women will be given two boxes of study supplements (one 4-week supply and a 4-week buffer) and receive counselling, as described above.

#### ANC follow-up visits

After enrolment, women will be seen by research staff every 4 weeks and encouraged to attend all recommended ANC visits. In Burkina Faso, these visits will coincide with routine antenatal care. In Pakistan, except for the 20<24 and 30<34 week visits, follow-ups will take place at the home. At each visit, adherence will be assessed by asking about supplement use on the prior day, including: whether the woman took each of the supplements, whether they were taken together or separately, at what time each of the supplements was taken, and whether each of the supplements was taken with or without food. Women will also be asked how many days in the past week they took each of the supplements. Finally, we will count and record the number of tablets remaining in the blister packs. Additional supplements will be dispensed so that women always have an 8-week supply. Staff will also collect morbidity information and abstract health card data on anthelminthic medication, sulfadoxine-pyrimethamine (Burkina Faso only), and low-dose aspirin. Providers at both sites will be trained to clearly record any blood transfusions, IV iron, and iron-containing supplements for data abstraction, and women will be asked to keep prescriptions and medication boxes. Information on all locally available iron-containing supplements, including photographs of packaging, was collected to facilitate data capture.

For visits in the windows of 20<24 and 30<34 weeks, women will also undergo a physical exam (including anthropometric measurements and blood pressure) and dietary intake assessment. The exam will include the venous blood draw, as described above. On-site Hb testing will be done using the HemoCue device for the purpose of identifying women with Hb<70 g/L and referring them for care while they are at the clinic. The primary trial outcome and safety outcome will be based on results of the CBC. These results will be reviewed after each visit to identify any cases of severe anaemia that were missed by on-site HemoCue testing. These women will be contacted and referred for care; their outcome data will be retained in the analysis. In Burkina Faso, malaria rapid diagnostic testing will also be done and, if positive, women will be referred for treatment.

#### Adherence visits

Home visits will be conducted by Community Health Workers in Burkina Faso (2–3 times during the first 2 weeks, then monthly) and by research staff in Pakistan (twice in the first 2 weeks, then monthly) to reinforce adherence messages. At each visit, women will be asked about whether they took the MMS tablet on that day and on the previous day, and at what time they took the MMS. The same questions will be asked for the calcium tablet. Staff will also review supplement blister packs to visually confirm adherence to the assigned regimen on the day of the visit. Information on women’s reasons for not taking their supplements as per instructions will be collected to understand barriers. Staff will also review key counselling messages and will provide additional targeted counselling for women who are non-adherent or who have questions about the intervention.

#### Birth visit

A visit will be conducted within 72 hours of birth to collect data on pregnancy outcome, maternal and infant vital status and infant sex. Measurements of maternal blood pressure with the Microlife Cradle VSA and infant weight to the nearest 10 g using the ADE M118600 baby scale (ADE Germany GmbH, Hamburg, Germany) will be done. A capillary blood sample will be taken by heel prick from the infant and tested on site for Hb using the HemoCue Hb 301 and ferritin using a quantitative immunochromographic test run on the Easy Reader+platform (Veda-Lab, Alençon, France) to inform our secondary outcomes (ie, Hb and iron status within 72 hours of birth). Newborns with Hb<110 g/L will be referred for care. Referrals will not be made based on ferritin results; however, these will be provided to the treating clinician in the event of referral for low Hb.

### Patient and public involvement

Participants and members of the study communities were not involved in the design of the trial. However, engagement has occurred through recruitment of local staff to support community sensitisation activities. Plans are in place to involve community members in dissemination of study findings to participants and other local stakeholders.

### Data management

During interviews, most data will be directly entered on tablets into electronic case report forms using REDCap software. Exceptions include names and contact information, which will be maintained only in hardcopy records at both sites. In addition, data collected by Community Health Workers as part of household visits in Burkina Faso will be collected on hardcopy forms and entered into REDCap by research staff. While ultrasound measurements will be entered into electronic CRFs, ultrasound images will be captured and temporarily stored on the ultrasound machines (MindRay DP-10 in Burkina Faso; MindRay M6 in Pakistan), with images transferred on a weekly basis to the local server for back-up. REDCap forms will be configured to include double data entry of unique identifiers and range checks for all continuous variables. All electronic data will be stored in a secure, access-restricted REDCap database. Where data are collected and stored on paper, staff will keep paper private, and forms secured during the workday. At field offices, the paper forms will be stored in locked trunks and cabinets. These local field offices will also be locked, and access will only be permitted to pre-approved study personnel. Data for analysis (largely de-identified) will be hosted on an encrypted cloud server, with daily back-up. The file storage system will be the main data repository for analytic data.

### Biospecimen analysis

Venous blood collected at the early-pregnancy (6<20 weeks), mid-pregnancy (20<24 weeks) and late-pregnancy (30<34 weeks) visits will be stored on ice packs for shipment in EDTA-treated vacutainers and either untreated or serum separator vacutainers. In Burkina Faso, EDTA-treated whole blood will be sent to the Kaya District Hospital for full haematology analysis using a Sysmex MODEL XN-1000 haematology analyser (Sysmex Corporation, Kobe, Japan) and, at the baseline visit, qualitative testing for haemoglobinopathies by agarose electrophoresis on a cellulose acetate strip using a Wincom DY-300 Electrophoresis Machine (Wincom Company, Changsha, China). Ferritin and CRP will be measured using immunoturbidimetric assays on a Biolis 30i Automated Clinical Chemistry Analyzer (Tokyo Boeki Medical System, Tokyo, Japan). An aliquot of serum will be shipped on dry ice to the Micronutrient Laboratory at the Johns Hopkins Bloomberg School of Public Health, where commercial immunoassay kits will be used to measure sTfR (R&D Systems, Minneapolis, Minnesota, USA), hepcidin (DRG International, Springfield, New Jersey, USA), and EPO (R&D Systems, Minneapolis, Minnesota, USA). A commercial radial immunodiffusion assay (Kent Laboratories, Bellingham, Washington, USA) will be used to measure AGP.

In Pakistan, CBCs will be obtained using a Sysmex XN-100 automated haematology analyser (Sysmex Corporation, Kobe, Japan); haemoglobinopathies will be assessed by HPLC performed on a BIORAD Variant II instrument; and malaria parasitaemia will be assessed by microscopy on thick and thin blood smears. Both haemoglobinopathy and malaria testing will be done at baseline only in Pakistan, to inform ancillary analyses on the aetiology of anaemia in this setting. Ferritin, sTfR and CRP will be measured by immunoturbidimetric assay and AGP by immunological agglutination/turbidimetric assay on a Cobas c 311 Automated Analyzer (Roche Diagnostics GmbH, Mannheim, Germany), EPO will be measured using a chemiluminescent assay on the Immulite-2000 platform (Siemens Healthcare Diagnostics, Tarrytown, New York, USA), and hepcidin by a commercial competitive binding immunoassay (DRG Hepcidin 25 bioactive HS ELISA kit, DRG International, Springfield, New York, USA).

Results of ferritin, malaria and haemoglobinopathy testing will be shared with women. Women with haemoglobinopathies will be referred for counselling and medical management and monitoring. As National Pregnancy Care Guidelines in Burkina Faso contraindicate iron supplementation during pregnancy in women with SS or SC haemoglobinopathies, we will apply this exclusion to both sites. They will be deemed ineligible for the trial based on a contraindication and treated as post-randomisation exclusions. Women who are AS or AC carriers will be eligible for the trial and informed of their carrier status. Results of all tests will be kept confidential by the study team, but women will be free to share results with their care providers.

### Statistical methods

The statistical analysis will be structured around three pre-specified estimands, defined in accordance with the ICH E9(R1) Addendum and described in online supplemental table 1. Anticipated intercurrent events and their handling strategies are specified in online supplemental table 2. Briefly, the primary estimand applies a treatment policy strategy across all randomised women (ITT); the secondary estimand applies a per protocol strategy restricted to adherent women; and the sensitivity estimand applies an analysis restricted to women who did not develop severe anaemia prior to outcome ascertainment (mITT). The analyses described below correspond to these three estimands.

For analysis of the primary outcome—Hb measured by haematology analyser at 30<34 weeks of gestation—we will apply all three estimands. For the per protocol analysis, we will use a two-tier approach to characterise adherence. The first tier will quantify the median pill count per monthly follow-up visit. The second tier will quantify the percentage of monthly follow-up visits and household visits where women self-reported taking calcium and MMS at the appropriate time on the previous day, that is, the time prescribed for their assigned study arm. The per protocol dataset will include subjects who consumed a median of ≥75% study supplements per month based on pill count and consumed supplements at the prescribed time on the prior day at ≥75% of visits. The mITT dataset will include subjects who were not diagnosed with severe anaemia (Hb 70 g/L) during follow-up period.

As treatment effects may vary between countries due to differences in the determinants of Hb concentration, we will use a two-stage approach to combine treatment effect estimates across countries. In the first stage, we will estimate country-specific treatment effects and 95% CIs using simple linear regression models with a dummy variable for allocation. We will treat these site-specific analyses as separate hypothesis tests and will not correct for multiple testing across site-specific analysis results. In the second stage, we will pool the country-specific effects. Since between-country heterogeneity in treatment effects cannot be estimated precisely with only two countries, we will present both fixed-effect and random-effects estimates across countries. The latter will be performed using the inverse variance approach with the between-country treatment effect variance estimated by the DerSimonian and Laird method. Country-specific results will be the primary basis for the NI decision; the pooled estimates are secondary summaries to present the range of plausible pooled effects without relying on an imprecise estimate of between-country heterogeneity or assuming a common effect across countries. In addition to the unadjusted analyses, we will conduct sensitivity analyses including the following baseline covariates: parity, body mass index, height and baseline values for Hb, ferritin, CRP and AGP. We will follow the same approach for the ITT, PP and mITT analyses. NI will be determined using the fixed-margin methods (figure 3). That is, if the lower limit of the 95% CI around the difference in Hb concentration between the intervention and control is greater than the NI margin of −3 g/L, the intervention will be deemed non-inferior. We will use both ITT and PP approaches. For NI trials, PP analysis provides a more conservative assessment; however, as differential adherence between arms is possible, PP analysis may introduce bias through differential post-randomisation selection based on adherence. Therefore, while both analyses will be examined for consistency, ITT will be considered primary. We will also explore effect modification based on receipt of any iron treatment, extracted from health cards, and dietary iron and calcium intakes. A *p* value<0.05 for the interaction term will be considered statistically significant.

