### Interventions

All participants will receive two daily supplements: (1) a UNIMMAP MMS, providing 30 mg elemental iron, and (2) a 500 mg elemental calcium supplement as 1250 mg calcium carbonate. In the intervention arm (the ‘together’ arm), women will be instructed to take both tablets together in the morning. In the control arm (the ‘separate’ arm), they will take MMS in the morning and calcium in the evening. Women in both arms will be told to take the supplements starting at enrolment (6<20 weeks’ gestation) until the end of the pregnancy.

UNIMMAP MMS will be sourced from Contract Pharmacal Corporation (Hauppauge, New York, USA). Calcium supplements will be sourced from CitraGen Pharmaceuticals (Fremont, California, USA). Bulk supplements will be co-packaged into arm-specific boxes (figure 1) by Remington Pharmaceuticals (Lahore, Pakistan), with barcoded labels to indicate lot numbers, the repackaging date, and the expiry date of repackaged supplements. Each box will contain four calendar blister packs with a 7-day supply of tablets. Study supplements will be stored in humidity and temperature-controlled pharmacies at each site until delivered to recruitment centres.

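### The per-protocol rule for the 30<34-week haemoglobin uses a median monthly pill count and sets no cut-off at the outcome draw, so it admits moderately adherent women and selects on behaviour after the outcome

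*Protocol article*

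**What the plan says.** The per-protocol set is defined in the protocol article under Statistical methods, in two tiers that must both be met.

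- Tier 1 is a pill count: "The first tier will quantify the median pill count per monthly follow-up visit". The threshold is that a woman "consumed a median of ≥75% study supplements per month based on pill count".
- Tier 2 is timing: the share of monthly and household visits at which "women self-reported taking calcium and MMS at the appropriate time on the previous day". The threshold is "and consumed supplements at the prescribed time on the prior day at ≥75% of visits".

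The outcome that this set serves first is "Hb measured by haematology analyser at 30<34 weeks of gestation". Under Interventions, supplements are taken from enrolment "until the end of the pregnancy". Table 3 schedules adherence recording at the interim visits after the late-pregnancy visit and again at birth. The per-protocol definition gives no date at which counting stops. The same section describes the sensitivity (mITT) estimand by reference to events before the outcome is ascertained, but gives no such limit for the per-protocol estimand.

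ITT is primary. The per-protocol analysis is examined for consistency with it, and the authors acknowledge that selection on adherence may bias it.

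**The concern.** Haemoglobin at 30<34 weeks can depend only on tablets taken before the blood draw. A rule that counts months and visits up to birth lets later behaviour decide who belongs in the analysis. It errs in both directions: a woman who followed her regimen until the draw and then stopped can be excluded, and one who followed it poorly until the draw and well afterwards can be included.

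The median adds a separate problem. Months with no intake do not lower it so long as more than half of the months are at or above the threshold, yet those months matter for iron status.

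The per-protocol analysis is there to show whether a non-inferior ITT result might reflect women not following their regimens. Partial adherers who enter the set dilute the contrast between arms and would be expected to move the per-protocol difference towards zero. In a non-inferiority trial that is the favourable direction, so agreement between ITT and per-protocol would reassure less than it appears to.

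**Working it through.** The plan gives no figure for the per-protocol set, so there is none to reproduce. The thresholds below are the plan's. The numbers of months and visits are assumptions, with ranges shown.

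**Tier 1: how little intake can give a median of 75%?**

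- Five monthly counts of 75, 75, 75, 0, 0%: the median is 75%, which passes. Total intake is (75 + 75 + 75) / 500 = 45%.
- With an odd number n of months, (n − 1)/2 of them can be empty: 2 of 5, or 3 of 7.
- Patterns in steps of 25%, with counting closed at the draw and 3 to 6 months before it: the lowest pre-draw intake that passes is about 45% to 56%. Closing the window therefore does not by itself cure the median.

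**Tier 2: 8 visits before and 5 after the draw (assumed)**

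Visits needed: 0.75 × 13 = 9.75, so 10 of 13.

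- Correct at all 8 before and none after: 8/13 = 62%, excluded.
- Correct on 50% of days before and 100% after: she needs 10 − 5 = 5 of the 8 earlier visits. P(X ≥ 5), X ~ Bin(8, 0.5), = (56 + 28 + 8 + 1)/256 = 93/256 = 36%.
- The same woman with counting closed at the draw needs 0.75 × 8 = 6 of 8. P(X ≥ 6) = (28 + 8 + 1)/256 = 37/256 = 14%.
- Correct on 25% of days before and 100% after: P(X ≥ 5), X ~ Bin(8, 0.25), = 2.7%.
- Correct on 50% of days throughout: P(X ≥ 10), X ~ Bin(13, 0.5), = (286 + 78 + 13 + 1)/8192 = 4.6%.

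**Other visit counts**

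| Visits before + after | Needed | Lowest share correct before draw | 50% before, 100% after: passes | Same, closed at draw | All correct before, none after |
|---|---|---|---|---|---|
| 6 + 4 | 8 | 67% | 34% | 11% | 6/10 = 60% |
| 7 + 5 | 9 | 57% | 50% | 6% | 7/12 = 58% |
| 8 + 5 | 10 | 63% | 36% | 14% | 8/13 = 62% |
| 12 + 5 | 13 | 67% | 19% | 7% | 12/17 = 71% |
| 15 + 5 | 15 | 67% | 15% | 2% | 15/20 = 75% |

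The fully adherent woman who stops after the draw is excluded in four of the five rows; in the last she sits exactly on the threshold and passes.

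**Both tiers together**

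The 36% is for tier 2 alone, and tier 1 must also be met. A woman who takes every tablet but times them correctly on only half of the pre-draw days has a pill count of 100%, so tier 2 is her only filter. A woman who misses tablets can also pass tier 1 if the missed ones are concentrated: 75, 75, 0% before the draw and 100, 100% after has a median of 75%, with 150/300 = 50% taken before the outcome. If she misses half evenly in each of those three months, her median is 50% and she fails.

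**The case against.** The case against is strong on several points, and most of it limits the size of the concern.

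- A reader might infer that women who took very little before the draw count as adherent. On tier 1 alone, with 3 months before and 2 after, 25% of the pre-draw supply is enough. The documents do not support this for the per-protocol set, because tier 2 is required jointly. Someone correct on 25% of days before the draw and 100% after passes tier 2 in 0.1% to 7.1% of cases over the visit counts above, if self-report is accurate.
- A reader might infer that the pill count is pooled over both tablets, so that full MMS with half the calcium reaches (100 + 50)/2 = 75%. The text does not say whether the count is pooled or per tablet. Tier 2 also asks about both tablets.
- A reader might want timing judged from the home-visit check, "Staff will also review supplement blister packs to visually confirm adherence to the assigned regimen on the day of the visit", in place of self-report. The strengths and limitations box says that some home visits are unannounced and made at mid-day. At that hour the together regimen can be confirmed in full, but the evening calcium of the separate arm is not yet due. The arms would be measured differently. Previous-day report covers the whole regimen in both.
- The estimand tables are in a supplement and a full SAP is cited; neither is shown. Either may already set a window. This stands as a caution. However, the article does state the rule itself, including the median and the share of visits without limit, and a window elsewhere would not remove the median.
- ITT is primary and the authors already warn about selection in the per-protocol analysis. This stands, and it keeps the point below the level of the main conclusion.

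**Conclusion.** The point holds in a limited form. As stated, the rule counts adherence after the primary outcome, and its pill-count tier tolerates empty months: 45% of tablets over five months is enough for that tier. Under both tiers with accurate self-report, the women wrongly admitted are moderate adherers, with roughly half to two thirds of pre-draw intake. Counting to birth and not to the draw raises the tier 2 pass probability of a woman correct half the time before the draw and always after it from about 14% to 36% at 8 + 5 visits. Over the visit counts tried, it is 15% to 50% with counting to birth, against 2% to 14% with counting closed at the draw.

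These figures rest on assumed visit and month counts, on independent days and on truthful reports. The effect on the haemoglobin difference itself was not estimated; it depends on how many such women there are. The weakness affects the per-protocol consistency check and leaves the primary ITT analysis and the sample size untouched. It is worth correcting because the better rule costs almost nothing.

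**What to change.** - Compute both tiers from enrolment to the date of the 30<34-week draw only, whenever the per-protocol set is used for outcomes measured at that visit.
- Replace the median with cumulative tablets taken divided by tablets due, requiring ≥75% for MMS and for calcium separately. This also settles whether the count is pooled.
- Keep previous-day self-report for the timing tier, and report blister-pack checks as supporting information only.
- Keep the present rule as a sensitivity analysis if wanted.

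The cost is a few sentences in the analysis plan and a small change in derivation code. Remaining tablets are already counted at the 4-weekly visits, and each supplement is asked about separately. The per-protocol set may be somewhat smaller and its interval slightly wider. Field work is expected to end in May 2027 and the code is broken only after all outcomes are assessed, so the change can be made while those responsible for the analysis are still blinded.
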